**Figure 2 F2:**
[figure not shown]
Overview of study procedures. FDG PET-CT fluorodeoxyglucose positron emission tomography computed tomography; FES 18F-Fluoroestradiol; SNP sentinel node procedure

#### Diagnostic work-up

After informed consent is obtained, an 18F-FDG PET-CT scan will be conducted (if not yet performed) to exclude macroscopic axillary lymph node involvement and distant metastases. If no marker has been inserted in the tumour during the diagnostic biopsy, an MRI compatible clip will be placed in the tumour to allow tumour localisation after neoadjuvant treatment. Additional tumour biopsies will be performed in the same session if separate consent has been obtained.

#### Treatment planning

An MRI with intravenous contrast (ie, gadolinium) and CT will be performed for RT treatment planning in supine position. The gross tumour volume (GTV), which is the breast tumour, is delineated on the simulation MRI. To account for microscopic disease, the GTV is uniformly expanded by 2 cm to create the clinical target volume (CTV), while excluding the first 5 mm below the skin and the entire chest wall including the pectoral muscles, not extending outside of the breast tissue. To account for delineation and setup uncertainties, the planning target volumes (PTV) are generated. The GTV is expanded by 3 mm, and the CTV is expanded by 3 mm (MR-linac) or 5 mm (CBCT-linac) to obtain the PTVs, PTV_GTV_ and PTV_CTV_, respectively.

Treatment techniques consist of intensity modulated RT (IMRT) on an MR-linac. On a conventional linac, IMRT or volumetric modulated arc therapy will be used. A single fraction involves two concomitant RT dose levels: 15 Gy to the PTV_CTV_ and 20 Gy to the PTV_GTV_. Adequate coverage of the target areas is determined by ensuring a mean dose (D_mean_) of 99–101% for PTV_GTV_ and PTV_CTV_, with at least 95% of the prescribed dose delivered to cover 98% of the PTVs. Additionally, restricting the dose to 107% or less in only 2% of the PTV_GTV_ is essential, while adhering to the prescribed doses for organs at risk (table 2). Failure to meet these predefined dosimetric constraints results in exclusion of the patient from the study.

**Table 2 T2:** Dose constraints organs at risk

Ipsilateral breast	D_mean_<5 GyPTV_CTV<25% of total breast volume
Contralateral breast	No constraint, dose as low as possible.
Heart	V _2.8Gy_<10%V _4.7Gy_<5%D_mean_≤1.2 Gy
Lungs	V_16Gy_ < 15 ccD_mean_≤2.66 Gy
Ipsilateral lung	V _6.2Gy_<10%V _12.4Gy_<0.5 cc
Chest wall	D_20cc_ < 16 GyAim for V_20Gy_ < 1 cc*Absolute constraint: V _22Gy_<1 cc, D_max_<30 Gy (cumulative dose)
skin	Dose as low as possible; aim for D_1cc_ < 12 Gy if this is not feasible aim for D_1cc_ < 16 Gy

*according to AAPM criteria, is expected to be feasible in patients with no late toxicity grade 2 or higher

CTV, clinical target volume; D, dose; GTV, gross tumour volume; PTV, planning target volume; V, volume.

#### RT treatment delivery

The single-dose PBI will be delivered within 14 days subsequent to the planning MRI and CT images. MRI-guided RT on an MR-linac will involve repeated breath-hold periods for patients exhibiting substantial tumour movement. Free breathing will be used when tumour position remains unaffected by breathing patterns. Real-time MRI tumour tracking will be used on a MRIdian. On the conventional linac, breath-hold periods will only be used for patients with left-sided tumours for optimal cardiac sparing. On conventional linacs, real-time position management and/or surface guidance will facilitate patient tracking. Additionally, patients will be asked to complete a questionnaire once (5 min) regarding comfort levels during treatment delivery (online supplemental material 1).

#### Preoperative follow-up

Approximately 3 (±one) weeks after single-dose PBI, a diagnostic MRI will be performed just prior to BCS, to assess the acute tumour response after RT. Radiological response is evaluated based on decrease in contrast uptake and decrease in diffusion restriction. The Response Evaluation Criteria in Solid Tumors (RECIST) criteria (V.1.1) are used to monitor tumour response. The MRI will be combined with collection of blood sample for isolation of peripheral blood mononuclear cells.

#### Breast-conserving surgery

BCS will be performed approximately 3 (±one) weeks after single-dose PBI. Axillary staging and treatment will be performed based on the decision of the multidisciplinary tumour board of the respective hospital according to standard of care. All patients will receive a prophylactic single dose (2 g) of Cefazolin 30 min prior to surgery, to prevent any wound infection. The surgical specimen will be examined by an experienced breast pathologist. Viable tumour cells will be assessed using H&E staining alongside the evaluation of cytokeratin antibody activity. Pathological response is assessed according to the residual cancer burden (RCB). RCB is calculated as a continuous variable (RCB calculator https://www3.mdanderson.org/app/medcalc/index.cfm?pagename=jsconvert3) and classified into four RCB classes indicating progressively larger residual disease burden^16^:

RCB-0 (RCB score 0, equivalent to pathologic complete response).RCB-I (RCB score ≥0–1.36, minimal burden).RCB-II (RCB score 1.37–3.28, moderate burden).RCB-III (RCB score >3.28, extensive burden).

The following parameters are required from pathologic examination to calculate RCB: the largest two dimensions (mm) of the residual tumour in the breast, average percentage overall tumour cellularity (invasive and in situ), average percentage of the carcinoma in and outside the tumour bed that is in situ, number of positive lymph nodes and size of the largest axillary metastasis (mm).

Furthermore, the frequency of patients presenting with DCIS within the surgical specimen will be documented. India ink will be used to mark the surface of the excised specimen to evaluate the surgical margins. Surgical margins will be described as the minimal microscopic tumour-free margin of invasive and in situ carcinoma (in mm) in the direction of the nearest surgical margin. In the case of involved surgical margins, a re-excision will be performed.

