The value of a repeat sentinel lymph node biopsy (SLNB) as a staging tool in patients with an IRBE is disputable. The risk of axillary lymph node metastasis in patients with an IRBE after previous BCS and SLNB is 26%.^31^ A meta-analysis showed that a repeat SLNB has a negative predictive value of 96.5% and a false negative rate of 4.1% for tumour negative nodes.^32^ In the SNARB study, 515 patients with an IRBE underwent repeat SLNB for axillary staging after a median recurrence interval of 10.5 years (0.4–31.8).^33^ In the primary setting, 203 (39.4%) patients underwent an SLNB and 278 (54%) underwent axillary lymph node dissection. The repeat SLNB could not identify the sentinel node in 239 (46.4%) patients.^33^ No significant difference was found in the 5-year recurrence-free survival between patients with an unsuccessful, tumour-positive or tumour-negative SLNB (p=0.543).^33^ Additionally, a recent retrospective cohort of 119 patients with an IRBE with negative lymph nodes on 18F-FDG-PET/CT who underwent repeat SLNB showed that repeat SLNB was successful in 66% of the patients and 8% had a tumour-positive sentinel node.^34^ The 10-year OS was comparable across patients with tumour-positive, tumour-negative and unsuccessful repeat SLNB (89% vs 89% vs 95%, p=0.701). Consequently, in the REPEAT study, a multidisciplinary tumour board will determine the axillary staging method. This also simplifies the treatment process with preoperative PBI and could reduce SLNB-associated morbidities.

Possible limitations of this prospective multicentre study are the relatively short follow-up. The reason for the 5-year follow-up is because of the primary outcome acute toxicity and the feasibility design of this study. Second, the interval between RT and surgery is too short to achieve a pathological complete response. Results from the ABLATIVE trial showed that the rate of PCR is higher after 8 months (48%) compared with 6 months (33%).^14^ This suggests, although patient numbers were small, that the RT may still kill tumour cells after 6 months. To ensure oncological safety in these patients with recurrent breast cancer, we chose an interval of 3 weeks for this feasibility study.

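### Pathological response is defined by full RCB, which needs nodal pathology that the design does not secure; a breast-only measure should carry the endpoint, and the RCB-I lower bound overlaps RCB-0

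*Protocol article*

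**What the plan says.** The Breast-conserving surgery section fixes the endpoint: "Pathological response is assessed according to the residual cancer burden (RCB"), as a continuous score and in four classes. It introduces the inputs with "The following parameters are required from pathologic examination to calculate RCB". The list covers residual tumour dimensions, cellularity and in situ percentage in the breast, and then "number of positive lymph nodes and size of the largest axillary metastasis (mm").

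The same section does not fix axillary surgery: "Axillary staging and treatment will be performed based on the decision of the multidisciplinary tumour board of the respective hospital according to standard of care". The Discussion explains why. It regards repeat SLNB as a doubtful staging tool in these patients and hopes that the chosen policy may spare some SLNB morbidity. It cites two cohorts:

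- 515 patients: "The repeat SLNB could not identify the sentinel node in 239 (46.4%) patients".
- 119 patients with negative nodes on FDG PET-CT: "repeat SLNB was successful in 66% of the patients and 8% had a tumour-positive sentinel node".

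On the classes, RCB-0 is a score of 0, equated with pathologic complete response. The next class is "RCB-I (RCB score ≥0–1.36, minimal burden").

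The Statistical analysis section treats pathological response descriptively.

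**The concern.** The endpoint calls for nodal pathology in every patient, but the design does not ensure it, and the article's own Discussion shows that it often cannot be obtained. Nodal status at entry (Table 1) does not fill the gap, because it is clinical and based on imaging, whereas the RCB inputs are to come from pathology.

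Two problems follow:

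- **Availability.** Patients without examined nodes either have no RCB or have one that counts an unexamined axilla as negative. In the first case, results come from a subset selected by hospital policy and by SLNB success. In the second, measured and assumed nodal status are mixed, and any error runs towards a lower RCB.
- **Construct.** Under Treatment planning, the clinical target volume stays within the breast tissue. A positive node therefore adds burden that the irradiation did not target, and the total score no longer isolates the response to preoperative irradiation.

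Separately, as printed, a score of 0 belongs to both RCB-0 and RCB-I, so complete response and minimal residual disease overlap.

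**Working it through.** **Inputs**

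| Input | Value | Source |
|---|---|---|
| Sentinel node not identified, 515-patient cohort | 239 | Discussion |
| SLNB success, 119-patient PET-negative cohort | 66% | Discussion |
| Positive sentinel node, same cohort | 8% | Discussion |
| Planned patients | 21, inflated to 25 for a 15% allowance | Statistical analysis |
| Share with SLNB attempted, q | not stated | assumption, varied |
| Share of failed SLNBs followed by other axillary surgery, r | not stated | assumption, 0 to 1 |

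**Step 1. Reproduce the article's figures.** 239/515 = 0.464, which matches the stated 46.4%, so success is s = 0.536. In the second cohort, failure is 1 − 0.66 = 0.34. The planned total also reproduces: 21/0.85 = 24.7, rounded up to 25.

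**Step 2. SLNB attempted in everyone (q = 1) and no further axillary surgery (r = 0).** The expected number without sentinel node pathology is N × (1 − s).

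- N = 25: 25 × 0.34 = 8.5 and 25 × 0.464 = 11.6, so about 9 to 12.
- N = 21: 21 × 0.34 = 7.1 and 21 × 0.464 = 9.7, so about 7 to 10.

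**Step 3. Let the boards omit SLNB in some patients.** The share without nodal pathology is 1 − q × s.

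| q (assumed) | s = 0.66 | s = 0.536 |
|---|---|---|
| 1.0 | 34% | 46% |
| 0.9 | 41% | 52% |
| 0.75 | 50% | 60% |
| 0.5 | 67% | 73% |

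Half or more of the patients lack nodal pathology once q falls below 0.5/0.66 = 0.76 or 0.5/0.536 = 0.93.

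**Step 4. Let other axillary surgery follow a failed SLNB.** The share becomes 1 − q × [s + (1 − s) × r]. With r = 0 this is the table above. With r = 1 it is 1 − q, which is zero if SLNB is attempted in everyone. The article gives neither q nor r.

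**Step 5. Positive nodes.** If 8% refers to all patients, 0.08 × 25 = 2.0 are expected. If it refers to successful procedures only, 0.08 × 0.66 × 25 = 1.3. Either way, about one or two patients would carry a nodal term from outside the target.

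**Step 6. Class boundaries.** RCB-0 contains the score 0, and RCB-I as printed runs from 0 inclusive to 1.36. Their intersection is the score 0. No assumption is needed here.

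**The case against.** The strongest reply is that this is a condensed article. How to handle a missing component of a descriptive secondary score is ordinary content for the full protocol or analysis plan, and neither is shown. That is right as far as it goes: the absence of a missing-data rule is not the point. What stands is that the article itself chooses an endpoint with required nodal inputs and, in the same section, a design that does not secure them.

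Some stronger readings are tempting but are not supported:

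- **A reader might infer that RCB cannot be computed at all without nodes.** Zero positive nodes could be entered for clinically node-negative patients. That would be an unstated assumption, but a number would result. The article does not say that this will be done.
- **A reader might infer that more than half the patients will certainly lack nodal data.** Only the 34% and 46.4% come from the article. Anything higher needs an assumed omission rate. The rates also come from other cohorts: in the larger one, 54% had had an earlier axillary dissection, and prior axillary surgery in this trial's patients is unknown.
- **A reader might infer that 8% of staged patients will have an inflated score.** The denominator of the 8% is unclear.
- **A reader might infer that pathological response is the reference standard for the MRI and biomarker work.** No section says so. Radiological response has its own criteria, and the Statistical analysis section only plans to explore overlap among response markers.

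It is also fair to say that the intended RCB-I class is obvious, and that the authors already accept that the interval is too short for complete response. The boundary is a small correction and adds no weight to the main point.

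**Conclusion.** The point holds as a mismatch between a stated endpoint and a stated design. If SLNB were attempted in all patients and succeeded as in the cited cohorts, about 9 to 12 of 25 (7 to 10 of 21) would have no sentinel node pathology. This assumes that those cohorts carry over to this trial and that no other axillary surgery follows a failure. For these patients full RCB would be missing or would rest on nodes assumed negative. In perhaps one or two others it would include disease outside the target volume. The overlap of RCB-0 and RCB-I at a score of 0 is a plain error.

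The reach is limited. The endpoint is secondary and descriptive. The primary toxicity endpoint and the sample size are untouched, and nothing here bears on how the axilla is managed. A change is still worthwhile, because in a trial of this size losing or assuming data in about a third to a half of patients would largely determine what the response summary shows.

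**What to change.** 1. Define pathological response in the breast only, for every operated patient: residual tumour dimensions, cellularity, in situ percentage, and breast pathologic complete response.
2. Report full RCB, score and class, only in patients with nodal pathology. Give the number evaluable and do not count unexamined axillae as negative.
3. Change the lower bound of RCB-I to greater than 0 (>0–1.36), so that a score of 0 falls only in RCB-0.

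The cost is a rewording of one secondary endpoint and one class boundary. The breast parameters are already to be collected, and no change to axillary staging is needed. The downside is less direct comparability with published full-RCB classes, which item 2 keeps for the evaluable subset.

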#### Follow-up

Patients with an indication for adjuvant endocrine therapy will start this treatment following BCS on prescription of the surgeon or medical oncologist. If microscopic findings (eg, Bloom-Richardson grade 3, tumour size >2 cm, triple negative or HER2-positive breast cancer) in the surgical specimen necessitate additional adjuvant systemic therapy, patients will receive appropriate treatment according to Dutch national guidelines.^17^ Annual clinical consultations, including a physical examination, with the attending radiation oncologist will be conducted up to 5 years following the second BCS. During these consultations, the radiation oncologist or physician assistant will assess both toxicity and cosmetic outcomes (figure 1). Additionally, patients will complete questionnaires (20 min) related to QoL and cosmetic outcomes at the following time points: baseline, preoperatively, 2 weeks, 6 weeks, 12 weeks and annually until 5 years after RT. Objective evaluation of cosmetic outcomes will be conducted through the capture of digital photographs at baseline, preoperatively, 1 year, 3 years and 5 years post RT. Consistent with the standard of care, radiological follow-up will comprise annual mammograms during the initial 5-year period similar to standard follow-up.

### Biobank

The diagnostic biopsy, the surgical specimen and blood samples will be stored (after additional informed consent by the patient) for a duration of 25 years at the Amsterdam UMC Central Biobank. Optional informed consent will be requested from the patient for two or three 14G tumour biopsies in order to investigate gene expression profiling in breast tumour tissue.

### Ethics and dissemination

This study will be conducted according to the Declaration of Helsinki (Fortaleza, Brazil, October 2013) and the Dutch Medical Research Involving Human Subjects Act (http://www.ccmo.nl). The study protocol has received approval from the Medical Research Ethics Committee of the Amsterdam University Medical Centre (NL85983.018.24), and has been registered in an international trial registry (ClinicalTrial.gov: NCT06640881). Approval has also been granted by the institutional review board of each participating centre. Subsequent to a written and oral explanation of the study, all participants are required to provide written informed consent prior to inclusion (online supplemental material 2). The results will be submitted/published in (peer-reviewed) journals and presented at scientific meetings.

### Patient and public involvement

Two patients advocates from the Dutch Breast Cancer Association reviewed the first draft of the study protocol. They were satisfied with the selected outcome measures and highlighted the importance of collecting oncological outcomes and QoL data. Additionally, they supported the proposal to make the additional tumour biopsy optional, aiming to minimise the treatment burden for participants. Newsletters including the results will be provided to participating patients.

### Quality assurance

In order to ensure the quality and integrity of the research data, an independent and qualified monitor will conduct centralised study monitoring at the Clinical Monitoring Centre of the Amsterdam UMC. The monitoring activities will adhere to national guidelines governing quality control for Dutch University Medical Centres.^18^

### Statistical analysis

The sample size calculation is based on the primary endpoint of the rate of grade 2 or higher acute treatment-associated toxicity within 90 days (skin toxicity, breast oedema, breast pain, chest wall pain, wound infection). We expect that 30% of our patients will experience ≥grade 2 acute toxicity following preoperative RT. An unacceptable proportion is considered if acute toxicity is observed in 50% or more of the patients. If, during the study duration, more than 50% of the first 10 patients develop ≥grade 2 acute toxicity, the study will be terminated. Therefore, based on the sample size calculation, which ensures that the CI does not encompass an incidence of 50%, a statistical power of 80% and a two-sided alpha of 0.05, a sample size of 21 patients is determined. Adjusting for a 15% allowance to accommodate patients deemed ineligible, the total required sample size is 25.

The assessment of the proportion of patients experiencing ≥grade 2 acute toxicity will be evaluated, and a 95% CI will be calculated. Grade 1 acute and late treatment-induced toxicity, PROMs and cosmetic results will be compared with baseline using linear mixed models for repeated measures. Radiological and pathological response, mastectomy rate, patient comfort during RT treatment delivery and oncological outcomes will be presented using descriptive statistics. The Kaplan-Meier method will be employed to quantify disease-free, breast cancer-specific and OS. Baseline T-cell levels will be analysed across patients to assess interpatient variability and intrapatient changes between baseline and post-treatment timepoints. Overlap in variance among different response markers will be explored. Additionally, the reproducibility of potential response markers, if applicable, will be investigated.

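### Two standards are given for the final toxicity result, an observed rate of 50% and a confidence interval excluding 50%, and the plan does not say which decides feasibility

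*Protocol article*

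**What the plan says.** All the relevant text is in the Statistical analysis section of the protocol article.

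- Expected rate: "We expect that 30% of our patients will experience ≥grade 2 acute toxicity following preoperative RT".
- Unacceptable result, worded on observed data: "An unacceptable proportion is considered if acute toxicity is observed in 50% or more of the patients".
- Early stop: "If, during the study duration, more than 50% of the first 10 patients develop ≥grade 2 acute toxicity, the study will be terminated".
- Basis of the sample size: a calculation "which ensures that the CI does not encompass an incidence of 50" (per cent), with "a statistical power of 80% and a two-sided alpha of 0.05, a sample size of 21 patients is determined". After the allowance for ineligible patients the total is 25.
- Final analysis: "The assessment of the proportion of patients experiencing ≥grade 2 acute toxicity will be evaluated, and a 95% CI will be calculated".

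The Background, Study design and Discussion sections all rest the feasibility judgement on this endpoint. None of them adds a decision rule.

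**The concern.** The first standard looks only at the point estimate. The second asks whether the data rule out a 50% rate. With 21 to 25 patients these are far apart, because the interval extends roughly 20 percentage points either side of the estimate. The analysis paragraph reports both the proportion and its interval but ties the conclusion to neither.

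Feasibility is the trial's primary claim. A result such as 10 of 21 (48%) is not unacceptable by the first standard and clearly fails the second. If the governing standard is not fixed beforehand, it can be chosen once the count is known.

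**Working it through.** **Inputs** (all from the Statistical analysis section): expected rate 0.30; unacceptable rate 0.50; 95% interval; 21 evaluable patients, 25 in total; stop if more than 5 of the first 10 have an event. X is the number of patients with an event, X ~ Bin(n, p).

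**1. The plan's own figure.** The half-width of a Wald interval at 30% must not exceed 0.50 − 0.30 = 0.20:

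n = 1.96² × 0.3 × 0.7 / 0.2² = 20.2, rounded up to 21. Then 21 / 0.85 = 24.7, rounded up to 25.

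So 21 follows from the interval standard as a precision calculation with no power term. With the stated 80% power and two-sided alpha of 0.05, the usual one-sample formula gives

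n = [1.96 × √(0.5 × 0.5) + 0.842 × √(0.3 × 0.7)]² / 0.2² = 46.6, so 47 (49 by exact binomial search).

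**2. Where the two standards part (n = 21).** An observed rate of 50% or more means at least 11 events. The 95% intervals around the boundary are:

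| Events | Rate | Wald | Wilson | Exact (Clopper-Pearson) |
|---|---|---|---|---|
| 5 | 23.8% | 5.6–42.0% | 10.6–45.1% | 8.2–47.2% |
| 6 | 28.6% | upper 47.9% | upper 49.96% | upper 52.2% |
| 7 | 33.3% | 13.2–53.5% | 17.2–54.6% | 14.6–57.0% |
| 10 | 47.6% | 26.3–69.0% | 28.3–67.6% | 25.7–70.2% |

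From 7 to 10 events the observed rate is below 50% and all three intervals include 50%. With 25 patients the band is 8 to 12 events: at 8 of 25 the upper limits are 50.3% (Wald), 51.6% (Wilson) and 53.5% (exact). Only 6 of 21 depends on the method. The expected count at the design rate is 0.3 × 21 = 6.3, so the boundary lies where the trial expects to land.

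**3. Probability of the undefined band** = P(X ≤ top) − P(X ≤ bottom − 1), without the early stop:

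- n = 21, p = 0.3: 0.974 − 0.551 = 0.42
- n = 21, p = 0.5: 0.500 − 0.039 = 0.46
- n = 25, p = 0.3: 0.983 − 0.512 = 0.47
- n = 25, p = 0.5: 0.500 − 0.022 = 0.48

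Counting the early stop, the n = 21 figures are both 39%, and the n = 25 figures are 43% and 40%.

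**4. What is at stake if an observed rate below 50% were taken as acceptable** (an assumption; the article does not say so). With the early stop,

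P(accept) = Σ over x = 0 to 5 of P(X₁ = x) × P(X₂ ≤ c − x),

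where X₁ ~ Bin(10, p), X₂ ~ Bin(n − 10, p), and c = 10 for n = 21 or c = 12 for n = 25. At p = 0.5 the stop itself has probability 0.377.

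| Rule | n | P(accept), true 50%, no stop | P(accept), true 50%, with stop |
|---|---|---|---|
| Observed < 50% | 21 | 50.0% | 42.9% |
| Observed < 50% | 25 | 50.0% | 41.7% |
| Exact upper limit < 50% (≤ 5) | 21 | 1.3% | 1.3% |
| Wald or Wilson upper limit < 50% (≤ 6) | 21 | 3.9% | 3.9% |
| Any of the three (≤ 7) | 25 | 2.2% | 2.2% |

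**5. Chance of success at a true 30% under the interval standard:** P(X ≤ 5) = 36% and P(X ≤ 6) = 55% at n = 21; P(X ≤ 7) = 51% at n = 25.

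**The case against.** The strongest reply is that there is only one threshold. The observed-rate sentence comes directly after the expected 30%, and the sample size follows from it. On that reading 50% is simply the unacceptable true rate set against the expected one, the interval criterion uses the same 50%, and the word for observed is loose drafting. This is a fair reading, so it goes too far to say that the plan contradicts itself. It does not remove the ambiguity: the sentence as written speaks of observed data, the early stop also uses an observed rate, and no sentence ties the final conclusion to the interval.

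Three stronger inferences are tempting, and the article does not support them.

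- A reader might infer that the plan would accept a treatment with a true 50% rate half the time. No sentence makes an observed rate below 50% acceptable, and under that assumed rule the early stop lowers the figure to 42–43%.
- A reader might put the undefined band at 6 to 10 events of 21, with probability 61% at the design rate. That holds only with exact limits, whereas 21 reproduces with Wald.
- A reader might count the unnamed interval method as a fault. That detail is commonly left to the analysis plan, which is not shown.

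It is also true that the interval will be reported, so readers would see that 10 of 21 does not exclude 50%. That tells them the uncertainty but not the trial's pre-specified verdict.

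**Conclusion.** The point holds as an ambiguity in the final decision rule. The only threshold stated for the final result is worded on the observed proportion, the trial is sized on an interval that excludes 50%, and nothing says which governs.

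The two standards leave 7 to 10 events of 21, or 8 to 12 of 25, without a verdict. At n = 21 that is a 42% chance if the design rate of 30% is right and 46% if the true rate is 50% (39% for both with the early stop). If the looser standard were applied, a true 50% rate would be accepted about 42–43% of the time after the early stop, against about 1–4% under the interval standard.

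These figures assume independent patients with a common event probability, 21 or 25 evaluable patients, and an early stop applied exactly as written and counted as non-acceptance.

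**What to change.** 1. State one final rule: feasibility is concluded only if the upper limit of the two-sided 95% confidence interval for the final proportion is below 50%. Any other result is reported as 50% not excluded.
2. Re-label the observed-rate sentence as the assumed unacceptable true rate, so that it cannot serve as a second final criterion.
3. Preferably name the interval method in advance, in the article or the analysis plan, because 6 of 21 passes with Wald or Wilson and fails with the exact interval.
4. Restate the power alongside the rule. The stated 80% does not hold under it: the chance of success at a true 30% is 36% (exact) or 55% (Wald or Wilson) with 21 patients and 51% with 25.

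The wording costs about two sentences and changes no procedure. The real cost is the disclosure in item 4: the sponsor must either accept and report the low chance of success or revisit the sample size (about 47 to 49 evaluable patients for 80%). The rule should be fixed before outcome data are reviewed.

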## Methods/design

### Study design

The REPEAT trial is a Dutch multicentre, phase II, single-arm prospective study at the Amsterdam University Medical Center (UMC) and Catharina Hospital Eindhoven in the Netherlands. The trial started in both centres in January 2025 and the estimated end date is December 2032. Eligible patients will be treated with ablative single-dose PBI followed by BCS after 3 (±one) weeks. At baseline (prior to RT) and prior to BCS, toxicity, PROMs and cosmetic outcome will be assessed. Additionally, a preoperative MRI will be performed 3 (±one) weeks following RT to evaluate the acute tumour response. The primary objective is to assess the feasibility of single-dose preoperative PBI and second BCS for an IRBE after previous BCT based on acute toxicity. The secondary objectives are to assess treatment-induced toxicity, radiological and pathological response, mastectomy rate, PROMs, cosmetic results, patient comfort during RT treatment delivery, oncological outcomes and RT-associated immune response markers (CD4, CD8 and FOXP3 expressing T cells) in blood and tumour tissue. All tumour tissue and blood samples of patients will be preserved at the Amsterdam UMC Central Biobank, location Vrije Universiteit Medical Center. This study design is based on the ABLATIVE study in patients with primary low-risk breast cancer, but with a shorter interval between RT and BCS (NCT05350722).^14 15^

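### With 21 evaluable patients and a true toxicity rate of 30%, the chance that the 95% CI excludes 50% is 36–55%, not the stated 80%

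*Protocol article*

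**What the plan says.** All the inputs stand in the Statistical analysis section of the protocol article.

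- Expected rate: "We expect that 30% of our patients will experience ≥grade 2 acute toxicity following preoperative RT".
- Unacceptable rate: "An unacceptable proportion is considered if acute toxicity is observed in 50% or more of the patients".
- Criterion behind the sample size: a calculation "which ensures that the CI does not encompass an incidence of 50" per cent.
- Operating characteristics and result: "a statistical power of 80% and a two-sided alpha of 0.05, a sample size of 21 patients is determined".
- Inflation: "Adjusting for a 15% allowance to accommodate patients deemed ineligible, the total required sample size is 25".
- Primary analysis: the observed proportion is assessed, "and a 95% CI will be calculated". The article names no interval method.
- Early stopping: if "more than 50% of the first 10 patients develop ≥grade 2 acute toxicity, the study will be terminated".

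The Study design section describes a "phase II, single-arm prospective study", so there is one proportion and no comparator.

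**The concern.** A 20-point difference between 30% and 50% is modest for a single proportion. Twenty-one patients looked too few for 80% power at a two-sided 5% level, and close to what a simple interval-width calculation would give.

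This is the only power figure in the article, and it supports the only primary endpoint, on which feasibility is to be judged. A reader told that power is 80% expects a 20% chance that the interval will still include 50% when the sponsor's own 30% is correct. If that chance is much larger, an interval reaching 50% would be an ordinary result of the sample size and would say little against the treatment.

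**Working it through.** **Inputs** (all from Statistical analysis): p1 = 0.30, p0 = 0.50, difference 0.20, two-sided alpha 0.05 (z = 1.96), power 80% (z = 0.8416), n = 21, allowance 15%.

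**1. Can 21 be reproduced?**

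With a power term:

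- Null and alternative variances: n = [(1.96 × √(0.5 × 0.5) + 0.8416 × √(0.3 × 0.7)) / 0.20]² = [(0.98 + 0.8416 × 0.4583) / 0.20]² = 46.6, so 47.
- Alternative variance only: n = (1.96 + 0.8416)² × 0.21 / 0.04 = 41.2, so 42.
- Null variance only gives 50, arcsine 47, and continuity-corrected 52.
- One-sided 5%, which would contradict the stated two-sided level, gives 37 and 33 for the first two formulas.

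None comes near 21.

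Without a power term, setting the Wald half-width around 30% to 20 points:

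- n = 1.96² × 0.3 × 0.7 / 0.2² = 20.17, so 21.
- Check: 0.30 + 1.96 × √(0.21 / 21) = 0.30 + 0.196 = 0.496, just under 50%.

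The inflation reproduces: 21 / 0.85 = 24.7, so 25.

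**2. What is the power at 21?**

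For each interval method, find c, the largest event count whose 95% upper limit is below 50%. Power is then P(X ≤ c) for a binomial with n patients and rate 0.30. The true one-sided error is P(X ≤ c) at rate 0.50.

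| n | 95% interval | c | Power at 30% | Error at 50% |
|---|---|---|---|---|
| 21 | Clopper-Pearson, Agresti-Coull, mid-P | 5 | 36.3% | 1.3% |
| 21 | Wald, Wilson, Jeffreys | 6 | 55% | 3.9% |
| 25 | all six | 7 | 51.2% | 2.2% |

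The 3.9% exceeds the nominal one-sided 2.5%, so part of the higher figure is bought with extra error. Applying the early stopping rule leaves the n = 21 powers at 36.3% and 55.0%. A 90% interval at n = 21 still has c = 6 and power 55%.

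**3. What would 80% take?**

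- By exact binomial calculation, power first reaches 80% at n = 40 (Wald), 43 (Wilson) or 49 (Clopper-Pearson). It stays at or above 80% from 45, 48 or 54.
- At n = 21, power is 80% only if the true rate is about 19% (c = 5) or 23% (c = 6).

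**4. Does the size ensure exclusion of 50%?**

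At 7/21 (33.3%) the Wald upper limit is 0.333 + 1.96 × √(0.333 × 0.667 / 21) = 0.535, and c is 5 or 6 for every method checked. So 7 events or more never exclude 50%. At a true 30%, P(X ≥ 7) = 1 − 0.5505 = 0.45.

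**The case against.** Several points on the other side have force, and some limit what may be concluded.

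- **The interval method may be settled in the full protocol or analysis plan.** True, but none of the six methods checked brings 21 patients near 80%. The concern is a figure that the article states, not a detail it leaves out.
- **A small feasibility study may be sized for precision.** It may. But then it should not claim 80% power.
- **The decision rule may rest on the observed proportion.** The sentence on unacceptable toxicity refers to toxicity observed in 50% or more of patients. Exclusion of 50% by the interval appears only in the sample-size sentence. On the observed-proportion reading, the chance of at most 10/21 events at a true 30% is 97.4%. This does not rescue 80%, but it does limit the consequence. A reader might infer that the trial is about as likely as not to fail; the article does not say that an interval reaching 50% counts as failure, so that goes too far.
- **The origin of 21.** A reader might take it as established that 21 came from a half-width calculation. The match is exact after rounding, but no formula is shown, so it remains an inference. The error in the power figure does not depend on it.
- **The result at 6/21.** A reader might cite this count, the nearest to 30%, against the claim of ensuring exclusion. The exact interval there is 11.3% to 52.2%, but Wald gives 9.2% to 47.9% and Wilson 13.8% to 49.96%. Only from 7/21 does the objection hold under every method checked.
- **Analysing all 25 patients.** A reader might expect this to recover the lost power. It raises the figure from 36% to 51% for the exact interval but lowers it from 55% to 51% for Wald or Wilson. Treatment planning also excludes patients who miss the dosimetric constraints, so the number irradiated may be below 25.

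**Conclusion.** The power statement is wrong as written. For the criterion in the sample-size sentence, a 95% CI lying below 50%, and a true rate of 30%, 21 evaluable patients give 36% (exact) or 55% (Wald or Wilson) rather than 80%. The interval would therefore include 50% with probability 64% or 45%, against the 20% a reader is led to expect. Reaching 80% by the usual formulas would take about 42 to 47 evaluable patients, roughly double the stated number.

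These figures assume independent patients with a common toxicity rate, and they apply to the interval-exclusion criterion only. The wording that exclusion of 50% is ensured is wrong under each usual interval method. The inflation from 21 to 25 is correct.

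**What to change.** In the Statistical analysis section, delete the 80% power claim and the word *ensures*, name the interval method, and describe 21 as a precision-based size. Suggested wording if the exact interval is chosen:

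> Twenty-one evaluable patients give a 95% confidence interval with a half-width of about 20 percentage points at an observed rate of 30%. With the Clopper-Pearson interval, the probability that the upper limit lies below 50% is 36% if the true rate is 30%, and reaches 80% only if the true rate is about 19%.

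If Wald or Wilson is chosen, the two figures become 55% and about 23%, and the true one-sided error of 3.9% should be given beside them. Say that these probabilities refer to the interval-exclusion criterion, so that they are not read as applying to the separate statement about the observed proportion.

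The change is to wording only, in the protocol and wherever the analysis plan repeats the claim. It needs no extra patients and touches no dose, schedule or stopping rule. The cost is a less favourable stated figure.
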